## Abstract

**Background:**

Variations in care models contribute to cancer pain being under-recognised and under-treated in half of all patients with cancer. International and national cancer pain management guidelines are achievable with minimal investment but require practice changes. While much of the cancer pain research over the preceding decades has focused on management interventions, little attention has been given to achieving better adherence to recommended cancer pain guideline screening and assessment practices. This trial aims to reduce unrelieved cancer pain by improving cancer and palliative doctors’ and nurses’ (‘clinicians’) pain assessment capabilities through a targeted inter-professional clinical education intervention delivered to participants’ mobile devices (‘mHealth’).

**Methods:**

A wait-listed, randomised control trial design. Cancer and/or palliative care physicians and nurses employed at one of the six participating sites across Australia will be eligible to participate in this trial and, on enrolment, will be allocated to the active or wait-listed arm. Participants allocated to the active arm will be invited to complete the mHealth cancer pain assessment intervention. In this trial, mHealth is defined as medical or public health practice supported by mobile devices (i.e. phones, patient monitoring devices, personal digital assistants and other wireless devices). This mHealth intervention integrates three evidence-based elements, namely: the COM-B theoretical framework; spaced learning pedagogy; and audit and feedback. This intervention will be delivered via the QStream online platform to participants’ mobile devices over four weeks. The trial will determine if a tailored mHealth intervention, targeting clinicians’ cancer pain assessment capabilities, is effective in reducing self-reported cancer pain scores, as measured by a Numerical Rating Scale (NRS).

**Discussion:**

If this mHealth intervention is found to be effective, in addition to improving cancer pain assessment practices, it will provide a readily transferable evidence-based framework that could readily be applied to other evidence practice gaps and a scalable intervention that could be administered simultaneously to multiple clinicians across diverse geographical locations. Moreover, if found to be cost-effective, it will help transform clinical continuing professional development. In summary, this mHealth intervention will provide health services with an opportunity to offer an evidence-based, pedagogically robust, cost-effective, scalable training alternative.

**Trial registration:**

Australian New Zealand Clinical Trials Registry (ANZCTR), ACTRN12618001103257. Registered on 3 July 2018.

**Electronic supplementary material:**

The online version of this article (10.1186/s13063-018-3152-z) contains supplementary material, which is available to authorized users.

## Background

Effective pain management cuts across professional boundaries with clinicians’ failure to routinely screen and assess for pain contributing to the burden of unrelieved cancer pain experienced by 39–66% of cancer patients [1]. To date, most research has focused on testing new cancer pain treatments, with little attention payed to strengthening cancer pain screening and assessment practices. Evidence suggests that implementing routine screening and assessment and managing pain in accordance with evidence-based guidelines can improve quality of care and outcomes for cancer pain [2–4].

Evidence of screening and assessment practices are increasingly being recognised as quality indicators of optimal cancer pain management internationally, with pain now recognised as the fifth vital sign and routinely recorded on inpatients’ observation charts [5]. The subjective nature of pain makes measuring patient-reported outcomes the optimal source of clinical information [6]. However, instead of routinely seeking a patient-reported Numerical Rating Scale (NRS) pain score, many clinicians adopt informal pain screening approaches [7] and/or fail to comprehensively assess their patients’ pain [8, 9]. A survey of Australian patients receiving community palliative care found that one-third experienced moderate to severe pain, restricting their activities over the preceding three days [10]. When this survey was repeated with a different cohort, a similar burden of unrelieved pain was reported [11].

It is recommended that a comprehensive pain assessment be undertaken for all cancer patients with an NRS pain score ≥ 2 [12, 13]. Determining the location, temporal pattern(s), exacerbating and/or relieving factors associated with the patient’s pain and ascertaining whether the pain has nociceptive or neuropathic origin(s) [14] is integral to determining a differential pain diagnosis and an individualised cancer pain management plan. Undertaking a comprehensive pain assessment is complex and too few clinicians have been formally taught how to assess across these pain domains, with most learning ‘on the run’, by observing their peers or through industry events. Yet, clinicians’ cancer pain assessment competencies [15], their understanding of the most suitable pain assessment tools, commitment and capacity to integrate pain assessment findings into clinical decision-making [16], communication skills and capacity to address their patients’ care needs within the context of multi-professional practice [17], all impact on their patients’ pain outcomes.

Unfortunately, many interventions aimed at improving clinicians’ pain assessment have had a limited effect on cancer pain outcomes [18–25]. The reasons for this failure are complex and varied and include failure to address the multiple barriers at the patient (i.e. failing to report the presence of pain), clinician (i.e. failing to adhere to recommended routine pain screening and assessment practices) [18] and organisational/system (i.e. accreditation and funding not linked to meeting pain management standards) levels. Most previous clinician-targeted cancer pain management interventions have been based on intuition, as opposed to being theoretically driven [26], which in part explains their ad-hoc success and limited transferability [16]. While a small number of previous interventions have focused on inter-professional education [18–23], not all have optimised the educational intervention ‘dose’ (strength) [18–22] or effectively managed the complexity of the intervention [20] and/or been underpinned by an evidence-based behavioural change framework [26, 27].

Despite the complexity of undertaking a comprehensive pain assessment, very few, if any, interventions have targeted cancer pain assessment as a distinct learning component, with most embedding screening and assessment into a broader cancer pain management learning package, privileging pharmacological cancer pain management practices [8]. In addition, few previous clinician targeted cancer pain management interventions have engaged both doctors and nurses, with most focusing exclusively on educating a single discipline as opposed to inter-professional practices [19]. Yet, the interdisciplinary nature of cancer and palliative care necessitates the implementation of targeted inter-professional learning strategies addressing pain assessment as a stand-alone construct [19]. Given this reality, there are opportunities to maximise the impact of any clinically focused cancer pain assessment behavioural change intervention by including evidence-based strategies, such as: (1) audit and feedback, which includes any summary of clinical performance over a defined period and can lead to potentially important improvements in practice [28]; (2) comprehensive interventions, which are more effective when addressing patients’ pain, especially when documentation and monitoring interventions are combined [18]; (3) more intense interventions involving extensive follow-up, a comprehensive educational program and greater resource allocation which are significantly more likely to impact positively on reducing cancer pain [20]; and (4) explicit application of theory to identify contextual conditions necessary for their success and enhance learning [26]. In addition, given the significant annual investments healthcare organisations make towards building clinical capabilities, few continuing professional development (CPD) activities are underpinned by evidence-based pedagogy and/or have been subjected to an economic analysis.

These gaps highlight the need to develop and test alternative strategies with a real potential to build cancer and palliative care clinicians’ cancer pain assessment capabilities, using effective and cost-effective pedagogically sound interventions underpinned by evidence-based behavioural change theories [27].

The trial protocol reported here adheres to the Standard Protocol Items: Recommendations for Interventional Trials (SPIRIT) checklist [29].

## Objectives

### Primary objective

To determine if a tailored mHealth intervention targeting clinicians’ cancer pain assessment capabilities is effective in reducing self-reported cancer pain scores, as measured by a NRS.

### Secondary objectives

To determine if the intervention:i.increases clinicians’ adherence to the Australian Cancer Pain Management in Adults Guidelines’ screening and assessment recommendations;ii.increases the quality of clinicians’ pain assessment documentation;iii.increases clinicians’ cancer pain assessment capabilities (knowledge and confidence); andiv.is cost-effective compared with standard cancer and palliative clinician CPD activities at reducing cancer patients’ reported pain scores from a healthcare systems perspective.

## Trial design

The study will use a phase III wait-listed randomised controlled trial (RCT) design, with individual cancer and palliative care clinicians as the units of randomisation (Fig. 1).

**Fig. 1 Fig1:**
[figure not shown]
Study *flow chart*

### Design considerations

The design of the study is a simple RCT with all participants considered as the basic randomisation unit and not nested in different sites. The justification for such consideration was based on the following two observations made during the pilot study: (1) there was virtually no cross-contamination among all participants, in that they had no knowledge about each other’s study status; and (2) there were no clustering characterisation across different sites such that participants could be considered as from a random sample [30]. Based on these observations, the study team opted to adopt the simple RCT design instead of a cluster RCT design.

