#### Pilot testing

The piloting phase tested the acceptability of the spaced learning intervention [30] and the feasibility of the proposed RCT [31]. Our uncontrolled pilot demonstrated a significant reduction in the mean patient-reported average daily numerically rated pain scores (0–10), between the pre-post test audit, of 1.5 (95% confidence interval [CI] = 0.7–2.3) [30]. In our pre-post test feasibility study, a positive effect was observed in all measures in the study. A larger adequately powered RCT is required to confirm these results given these previous studies had insufficient power to demonstrate statistical significance. These pilot study results have informed the proposed RCT sample size [30, 31]. This manuscript focuses on the protocol for the evaluation phase, which aims to determine if a tailored online spaced learning intervention that increases clinicians’ cancer pain assessment capabilities translates into a clinically significant reduction in cancer and palliative care patients’ NRS pain scores.

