### Outcomes

#### Primary outcome measure

The primary outcome measure will be at the patient level and concern the probability that a tailored mHealth performance feedback intervention will translate to a clinically meaningful reduction in the mean change in the pain NRS (0–10) scores, from admission to census date. A cut-off of a two-point difference or 30% reduction in pain intensity on a NRS is considered to represent a clinically important difference [38].

As this is a pragmatic trial, all pain NRS scores will be captured during the chart audit process from the patients’ medical records, thus negating the need for patient consent. The NRS is the optimal brief measure of pain severity on the basis of compliance rates, responsiveness, ease of use and applicability; it is also recommended by the Australian Cancer Pain Management in Adults Guidelines [12]. The inter-rater reliability of the chart auditors will be calculated using: Kappa statistics for categorical variables; and the Bland–Altman method of plots and limits of agreement for continuous variables will be used to determine the degree of agreement between chart auditors [39]. A waiver of patient consent has been authorised by the Human Research Ethics Committee (HREC) to include documented de-identified pain screening and assessment data from all patients receiving care from the participating units/sites during the a priori defined audit periods at Times 1–3, to avoid selection bias.

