##### Chart audit data

Patient-reported pain NRS scores and clinicians’ adherence to pain screening and assessment guidelines will be extracted from patients’ inpatient/ambulatory care medical records (electronic and/or paper-based). The chart audit tool developed, tested and refined during the pilot studies will be adopted to ensure standardised data collection. Medical records of all patients in the participating units, over 30 consecutive calendar days, will be screened for audit at each study time period (T1–T3). This will facilitate capturing chart audit data within the same duration across all participating units at each study time point. Documented patient-reported pain NRS scores and guideline adherence data will be collected by trained project officers.

Eligible medical records (chart audit) will include all patients who during the three audit periods: (1) have a primary diagnosis of cancer; 2) present for cancer treatment at a participating centre and/or are referred to a specialist cancer/palliative care service; and (3) have pain at the time of first visit/appointment/admission or develop pain during the audit period. In addition to capturing patients’ basic demographics such as age, gender, length of hospital stay, medical diagnosis, and cancer and pain treatment(s), the chart audit will also capture: patients’ pain scores on admission to the service; their pain scores at discharge and/or audit date, depending on which occurs first; clinicians’ documentation pain screening/assessment actions; and whether the clinician who documented the pain screening/assessment actions was an intervention participant or non-participant (T2 and T3 only).

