#### Statistical methods

##### Statistical analysis plan

An intention-to-treat analysis will be applied to all primary and secondary outcomes. Missing data will be imputed using Multiple Imputation by Chained Equations. Should an imbalance in clinicians’ characteristics be found between groups at baseline, these characteristics will be included in the final analyses as covariates. A significance level of 5% will be adopted for refuting all test hypotheses. The intervention and wait-listed control arms will be compared on the primary and secondary outcome measures.

The primary endpoint (reduction in mean pain NRS scores) will be analysed using the Linear Mixed Method with a repeated measures approach and possible adjustments to patients’ and staff characteristics to compare the mean change in patient pain NRS scores from admission to discharge or audit date between the intervention and control groups across different time points.

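### Clinicians are randomised within shared units but the primary outcome is one pain change per patient, so the comparison of arms is not defined and the unqualified 90% power is not supported

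*Protocol article*

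**What the plan says.** - **Randomisation.** Trial design describes a wait-listed RCT "with individual cancer and palliative care clinicians as the units of randomisation". Design considerations adds that "The design of the study is a simple RCT with all participants considered as the basic randomisation unit and not nested in different sites".
- **Justification.** Design considerations relies on two pilot observations. The first is that "there was virtually no cross-contamination among all participants, in that they had no knowledge about each other"'s study status. The second is that no clustering across sites was seen. One pilot reference is cited.
- **That pilot.** Pilot testing, citing the same reference, says: "Our uncontrolled pilot demonstrated a significant reduction in the mean patient-reported average daily numerically rated pain scores". The change was 1.5 (95% CI 0.7 to 2.3), before against after.
- **Outcome.** "The primary outcome measure will be at the patient level", as the change in NRS pain from admission to the census date.
- **Source of patients.** "Medical records of all patients in the participating units, over 30 consecutive calendar days, will be screened for audit at each study time period". Eligible records may be inpatient or ambulatory.
- **Link to clinicians.** At T2 and T3 only, auditors code whether each documented screening or assessment action was by an intervention participant or a non-participant. They match chart signatures to consent forms and check the work roster.
- **Analysis.** Intention-to-treat, with a "Linear Mixed Method with a repeated measures approach" and possible adjustment for patient and staff characteristics, comparing patients' pain change between the two arms.
- **Sample size.** 35 clinicians per arm for 90% power at 5% and a difference of 1.5 (+ 2.0), raised to 45 per arm. Patients per clinician, ICC and dilution are not mentioned.

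**The concern.** Randomisation assigns clinicians to arms. The primary comparison needs patients to have an arm, and nothing in the article gives them one. A code on each documented action labels a chart entry. It does not say to which arm an admission-to-discharge pain change belongs when several clinicians wrote in that chart, or when none of them was enrolled.

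Three things follow. First, the primary estimand is open, and the linking rule could be chosen after auditors who know the allocation have collected the data. Second, if patients receive care from both arms, the contrast between arms is smaller than the effect of the training itself, and a null result could not be told apart from dilution. Third, the power statement uses an effect that was not measured as a concurrent difference between clinicians working in the same units.

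**Working it through.** **1. Does the stated justification reach the problem?** Two statements stand side by side. Design considerations reports that "there was virtually no cross-contamination among all participants", in the sense that clinicians did not know each other's study status. Pilot testing calls the cited pilot uncontrolled.
- Without a control arm, contamination between arms could not be observed.
- Not knowing a colleague's status says nothing about whether two clinicians treat the same patient.
- Absence of clustering across sites says nothing about sharing of patients within a unit.

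**2. The plan's own figure.** Inputs from Sample size: difference 1.5, SD 2.0 (assumption: + 2.0 is a plus-minus sign lost in conversion), alpha 5% (assumed two-sided), power 90%.
- n per arm = 2 × [2.0 × (1.960 + 1.282) / 1.5]² = 37.4, so 38 (t-test: 39). The plan states 35.
- At 35 per arm: SE = 2.0 × √(2/35) = 0.478; 1.5/0.478 = 3.137; power = Φ(3.137 − 1.960) = 88% (t-test: 87%).

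So 35 is a near miss for 90% with no dilution at all. This gap is minor and is not the basis of the point.

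**3. Effect of dilution, one patient outcome per clinician.** Let f be the share of the 1.5-point contrast that survives shared care. The document gives no f, so these are assumptions (35 per arm, SD 2.0, t-test power):

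| f | contrast | power |
|---|---|---|
| 1 | 1.5 | 87% |
| 0.75 | 1.125 | 64% |
| 0.5 | 0.75 | 34% |

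**4. The same dilution with several patients per clinician.** Assume 10 audited records per clinician, each patient shared by two clinicians, ICC 0.05 and f = 0.5.
- Distinct patients per clinician: 10/2 = 5, so 35 × 5 = 175 per arm.
- Design effect: 1 + (5 − 1) × 0.05 = 1.20. Effective n: 175/1.20 = 145.8 per arm.
- SE = 2.0 × √(2/145.8) = 0.234; 0.75/0.234 = 3.202; power = Φ(3.202 − 1.960) = 89%.

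This is crude: dividing the records by two does not model the correlation created when one patient counts towards clinicians in both arms. It is enough to show that the same half-sized contrast gives about 34% or about 89% power, depending on quantities that the plan does not state.

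**The case against.** The strongest reply has four parts.

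- **Shared care is inferred.** The article nowhere says that patients are treated by both arms. Ambulatory records are included, and there one clinician may do the whole assessment. This stands as a limit. On inpatient wards, with individual randomisation inside the unit, all patients audited and authorship tracked action by action, the inference is still strong.
- **The power loss is not demonstrated.** A reader might infer that true power is only 34%, or lower. The document does not support that: the figure needs one patient per clinician and half the contrast lost. Several unshared patients per clinician could make 35 clinicians ample; at 5 patients each and ICC 0.05, 45 patients per arm, or 9 clinicians, would suffice without dilution. This stands.
- **The model may handle clustering.** A reader might also infer an inflated type I error from treating one clinician's patients as independent. The article names a mixed model and does not say that clinician is ignored; the random effects may be in an analysis plan not shown. Likewise, repeated measures can refer to clinician or site, so the term is not itself an error. Both points stand. No random-effects structure, however, gives a patient an arm or undoes dilution.
- **The pilot effect may already be diluted.** If only some staff took part in the pilot, 1.5 already includes some dilution. That is possible and cannot be checked here. It remains a before-after change without controls.

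**Conclusion.** The point holds as a design mismatch, not as a proven figure for lost power. The unit of randomisation and the unit of the primary outcome differ, the article names a comparison of patients between arms without a workable link from patient to arm, and the reason given for the simple design cannot carry it. These rest on the text.

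That the contrast will be diluted rests on shared care, which is likely on wards and of unknown extent. The unqualified 90% is unsupported: it is 87–88% before any dilution, under a two-sided test and SD 2.0, and the planning effect equals an uncontrolled pre-post change. How far power falls depends on the sharing fraction, patients per clinician and ICC, none of which is given. The definition of the comparison needs to be settled before T2 data are seen.

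**What to change.** 1. **Statistical analysis plan section.** Before any T2 data are seen, fix a rule that links each patient's pain change to an arm or to a degree of exposure. It should not rest solely on who chose to document, because documentation is what the intervention aims to change. Roster exposure at unit or shift level is one option where it can be obtained; the article uses rosters only to help identify signatories at T2 and T3, so availability must be checked. State how patients with no enrolled carer are handled. Include clinician random effects (multiple membership where care is shared) and site, with audit period as a between-patient factor.
2. **Sample size.** Replace the unqualified 90% with power over a stated range of dilution, patients per clinician and ICC.
3. **Design considerations.** Withdraw the no-contamination justification, and state dilution through shared patients as a limit on interpreting a null result.
4. **Allocation (optional).** Stratify the permuted blocks by site. This does not address shared patients.

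The cost is a more complex model, some extra recording during the audit and a less favourable stated power. None of this removes dilution; it defines the comparison and makes the limit visible.
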